#### **E. Randomization and Blinding**

Randomization was performed using a computer-generated random numbers table with a block size of 6 and a 1:1:1 ratio after stratification according to the type of surgery and age. Allocation was sequentially numbered and sealed in opaque

---

envelopes by the corresponding author. The anesthesiologists opened the envelopes 10 min before the emergence procedure. Because of the nature of the intervention, full blinding of all study personnel was not feasible. However, to minimize bias, we attempted to blind patients, practitioners (where possible), research assistants, and data analysts. It was not feasible to blind the PACU anesthesiologists and nurses. To achieve patient blinding, during the informed consent process, we described all interventions as anesthesia emergence positions, and we explained that depending on group allocation, patients may receive different emergence positions during anesthesia emergence. We additionally performed an analysis of blinding success of patients using Bang's Blinding Index.

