#### **F. Sample Size Calculation**

The sample size for the primary outcome of this study was calculated with continuity correction, and was based on a ratio of exposed (combined 15-degree and 30-degree SRP) to unexposed (supine positioning) groups of 2:1. According to our pilot study, the frequency of hypoxaemia was 46% in the unexposed group, with a 26% relative (12% absolute) reduction in the exposed group. Assuming a two-tailed type I error rate of 5%, a sample size of 620 was needed to give greater than 80% power to detect a decrease in the incidence of hypoxaemia from 46% in the supine positioning group to 34% in the combined 15-degree and 30-degree SRP groups. Finally, we planned to recruit 700 patients to compensate for dropouts. The sample size calculation was conducted using the PASS 11.0 software (NCSS LLC).

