#### **G. Statistical Analysis**

Continuous variables were presented as mean (SD) or median (interquartile range, [IQR]), depending on whether the data was distributed normally or not. Categorical variables were presented as a number (percentage). The normal distribution of data was evaluated using the Shapiro–Wilk test, and the Levene method was used to test the homogeneity of variance. Differences in repeated measures variables were analysed by repeated-measures analysis of variance. Continuous outcomes were

analysed with one-way analysis of variance (ANOVA) or Kruskal-Wallis test. Categorical variables were tested using  $\chi^2$  test or Fisher's exact test. The primary analyses were performed according to the intention-to-treat (ITT) principle. Modified ITT (mITT) and per-protocol (PP) analyses were also performed as sensitivity analyses for the primary outcome. Results of primary and secondary outcomes were reported as relative risk (RR) or between-group difference with 95 % CI, the absolute risk reduction (ARR) and Number needed to Treat (NNT) were also calculated, with 95% CI. Kaplan-Meier curves were used for the time to first experience hypoxaemia. When an overall intervention effect was detected ( $P < 0.05$ ), the Bonferroni correction for multiple pairwise comparisons would be performed. To handle missing data, multiple imputations by chained equations was used, assuming missing data are missing at random. Imputation for continuous data was performed by predictive mean matching, logistic regression for binary variables. The number of imputations was 5. Convergence of the multiple imputation algorithm and the results of the imputation were checked. Imputations were performed with the R MICE package (J Stat Software. 2011;45(3):1–67.). Analyses were then performed on each of the imputed data sets and pooled according to Rubin's rules. As a post hoc sensitivity analysis, we used a logistic regression model simultaneously entering: age, BMI, current smoking status, chronic pain needing opioids, ARISCAT score (Assess Respiratory Risk in Surgical Patients in Catalonia), CCI (Charlson Comorbidity Index), surgery time, intraoperative opioid consumption, and the use of a nasogastric tube. R version 4.1.1 was used for statistical analysis, and analysis items with 2-sided  $P < 0.05$  were considered statistically significant.

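### The Bonferroni step after a significant overall three-arm test is valid but stricter than needed, and costs about 11 points of power per angle if each angle has the planned 34% rate.

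*Protocol*

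**What the plan says.** Protocol section E randomises to three arms (supine, 15 degrees, 30 degrees) with "a block size of 6 and a 1:1:1 ratio after stratification".

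Section G tests categorical outcomes with a chi-square or Fisher's exact test. Pairwise comparisons follow only if the overall effect has P<0.05, and then "the Bonferroni correction for multiple pairwise comparisons would be performed". It does not say how many comparisons are counted, does not limit the rule to particular outcomes, and gives no reason for using both steps.

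Section F sizes the trial for a different contrast, with a "ratio of exposed (combined 15-degree and 30-degree SRP) to unexposed (supine positioning) groups of 2:1", at an uncorrected two-sided 5%. The planned fall is "from 46% in the supine positioning group to 34% in the combined 15-degree and 30-degree SRP groups". No rate and no power are given for either angle alone.

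**The concern.** The pairwise step is the only place where the two angles are judged separately. The protocol's objectives concern different degrees of tilt, and its section on preliminary studies notes a lack of evidence on which angle is suitable.

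Each pair passes two multiplicity controls in turn: an overall test at 5%, then a threshold of 0.05/3 = 0.0167. With three arms, either control is enough by itself. The second lowers the chance of showing a real benefit of one angle without being needed to keep the family-wise error at the usual level. An angle that works could then be reported as not shown to differ from supine.

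**Working it through.** **1. Reproduce the planned size.** Inputs from section F: 46% and 34%, ratio r = 2, two-sided 5%, 80% power, "calculated with continuity correction". The pooled rate is (0.46 + 2 × 0.34)/3 = 0.38.

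Uncorrected supine group: n = [1.96·√(3 × 0.38 × 0.62) + 0.8416·√(2 × 0.46 × 0.54 + 0.34 × 0.66)]² / (2 × 0.12²) = (1.648 + 0.715)²/0.0288 ≈ 193.8.

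With continuity correction: (n/4)·[1 + √(1 + 2 × 3/(193.8 × 2 × 0.12))]² = 48.45 × (1 + 1.0626)² ≈ 206.1, so 207 supine and 621 in all. Power at 620 is 80.1%. The protocol's figure ("a sample size of 620 was needed to give greater than 80% power") is confirmed. Per arm, 620/3 ≈ 207 and the recruitment target of 700/3 ≈ 233.

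**2. Why the overall test suffices with three arms.** There are three pairwise nulls, and if any two are true, all three arms are equal.
- All arms equal: a false claim needs a false-positive overall test, which has a 5% chance.
- Arms not all equal: at most one pairwise null is true, and it is tested once at 5%.

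This is strong control for one outcome at one time point. It does not extend to four or more arms.

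**3. Family-wise error by simulation** (400,000 trials per setting; 2-df chi-square overall test, then pairwise chi-square tests; Monte Carlo standard error at most √(0.25/400,000) = 0.08 points).
- Overall test, pairs at 5%: about 5.0% to 5.1% with all arms equal. With one arm different, 4.6% to 5.3% near the plan's rates, and about 5.4% in an extreme setting with one arm at 5%. The excess is the discreteness of a single chi-square test, not multiplicity.
- Overall test plus Bonferroni over three: about 4.2% to 4.4% with all arms equal; about 1.5% to 1.8% with one arm different.
- Bonferroni over three with no overall test: at most 4.7%.
- No control at all: 12% to 13% with all arms equal.

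**4. Power.** Check on one pair with no overall test, 46% against 34%, 207 per arm: the null standard error is √(2 × 0.40 × 0.60/207) = 0.0482 and the alternative one is √((0.2484 + 0.2244)/207) = 0.0478. At 5%: Φ[(0.12 − 1.960 × 0.0482)/0.0478] ≈ 70.4%. At 0.0167: Φ[(0.12 − 2.394 × 0.0482)/0.0478] ≈ 53.9%.

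Simulated power with the overall test in place (rates are supine/15/30 degrees; losses taken before rounding):

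| Rates (%) | Per arm | Shown better than supine | As written (three pairs) | Pairs at 5% | Loss |
|---|---|---|---|---|---|
| 46/34/34 | 207 | a given angle | 54.1% | 65.0% | 10.9 |
| 46/34/34 | 207 | both angles | 37.6% | 56.2% | 18.6 |
| 46/34/34 | 233 | a given angle | 59.7% | 71.0% | 11.3 |
| 46/34/34 | 233 | both angles | 43.8% | 62.8% | 19.0 |
| 46/36/32 | 207 | 15 degrees | 37.2% | 52.6% | 15.4 |
| 46/46/34 | 207 | 30 degrees | 54.0% | 64.1% | 10.1 |
| 46/40/34 | 233 | 15 degrees | 14.0% | 24.5% | 10.4 |
| 46/40/34 | 233 | 30 degrees | 59.5% | 64.3% | 4.8 |

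Only 46/34/34 and 46/36/32 average to the planned 34%; the last two patterns are sensitivity settings. If Bonferroni counts only the two comparisons with supine, power at 46/34/34 is 58.3% (207 per arm) and 65.0% (233 per arm), a loss of 6.6 and 6.0 points.

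**The case against.** **The rule is not an error.** This stands. Overall test plus Bonferroni keeps the family-wise error below 5%. The point is about efficiency.

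**The planned power is untouched.** This also stands. A reader might infer that the trial falls short of its stated 80%. Section F does not support that, because its power is for supine against both angles combined at an uncorrected 5%, and the protocol claims none for a single angle. Dropping Bonferroni would not make each angle adequately powered either: 65% and 71% remain below 80%.

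**The second correction buys something.** A reader might infer that the power is given up for nothing. It is not: when one pair truly does not differ, its false-positive rate is about 1.7% rather than 5%. That is protection below the nominal level, which the protocol does not ask for. Bonferroni would also serve simultaneous intervals, but section G asks only for 95% intervals.

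**The argument does not cover every outcome.** This is the objection with most force. Section J records vital signs at six time points, and pain, lung mechanics and blood gases at several. If arms were compared at each time, one vital sign would give 6 × 3 = 18 pairs. If one arm differed at one time only, two pairs would be real differences and 16 nulls would be true, so the step allowing at most one true null fails. The protocol does not say that pairs are tested at each time, but deleting Bonferroni everywhere would leave that case uncontrolled.

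**Timing.** Section G is written largely in the past tense and mentions a post hoc analysis. Relaxing a threshold after results are known would need open labelling.

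**Conclusion.** The point holds as an efficiency improvement for the primary outcome and other outcomes measured once. Under the natural reading (three pairs counted, 34% at each angle), the second correction costs about 11 points of power per angle and about 19 points for showing both angles.

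The figure of 11 is conditional. The protocol gives neither the rate at each angle nor the number of comparisons. Other splits examined give about 5 to 15 points, and counting two pairs gives 6 to 7; an angle with a very large effect would lose less, since its power is near 100% either way. The calculation takes the overall test to be the three-group chi-square. The error-control argument needs only that it be a 5% test of equality of all three arms. Control is within each outcome, not across outcomes.

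**What to change.** In section G, for the primary outcome and other outcomes measured once, replace the Bonferroni sentence with: *If the overall three-group test is significant at two-sided 5%, each of the three pairwise comparisons is tested at two-sided 5% (closed test for three groups).*

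Add that a multiplicity correction is kept wherever arms are compared at several time points (vital signs, pain scores, lung mechanics, blood gases), and state how many comparisons it counts.

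The cost is a short text change, with no extra patients or data. The downside is that a single true null pair is tested at 5% instead of about 1.7%. If outcome data have already been seen, label the change post hoc and report the Bonferroni results alongside.

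### Five imputations leave a borderline overall P value, and hence the gate to the pairwise tests, noticeably dependent on the random seed; raising the number is a minor, free improvement

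*Protocol*

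**What the plan says.** Protocol section III.G (Statistical Analysis) makes intention to treat the primary approach: "The primary analyses were performed according to the intention-to-treat (ITT) principle". For missing data, "multiple imputations by chained equations was used, assuming missing data are missing at random", with "logistic regression for binary variables". It then fixes the count: "The number of imputations was 5". On pooling it says "Analyses were then performed on each of the imputed data sets and pooled according to" Rubin's rules. The same section sets a gate. "When an overall intervention effect was detected" at P < 0.05, "the Bonferroni correction for multiple pairwise comparisons would be performed".

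Section III.F (Sample Size Calculation) needs 620 patients and adds a margin: "we planned to recruit 700 patients to compensate for dropouts". The protocol gives no expected rate of missing primary outcomes. It says that convergence and the imputation results were checked, but it does not mention the simulation error that comes from a finite number of imputations.

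**The concern.** Each imputed dataset contains random draws, so a pooled estimate from a small number of them carries simulation noise. Rubin's rules allow for that noise on average, so the inference stays valid. They do not stop a single pooled P value from changing when the seed changes. With 5 imputations the shift can be large enough to carry a result across 0.05.

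This matters here because the plan uses 0.05 as a hard switch. The same P value decides the primary conclusion and whether the 15-degree and 30-degree positions are each compared with supine. The Background lists the appropriate tilt angle among the open questions. The trial is sized for only a little over 80% power, so a result near the threshold is a realistic possibility.

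**Working it through.** **Inputs from the protocol.** Event rates of 46% (supine) and 34% (combined tilted groups), two-sided 5%, power above 80%, 2:1 sizing ratio with continuity correction, 620 needed, 700 recruited (III.F); 1:1:1 randomisation, so about 233 per arm (III.E); m = 5, logistic imputation, Rubin pooling, overall P < 0.05 as gate (III.G).

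**Step 1: reproduce the plan's own figure.** With d = 0.12, r = 2 and pooled rate (0.46 + 2 × 0.34)/3 = 0.38:

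- Uncorrected control size = [1.96 × √(1.5 × 0.38 × 0.62) + 0.8416 × √(0.46 × 0.54 + 0.34 × 0.66/2)]² / 0.12² = (1.165 + 0.505)² / 0.0144 ≈ 193.8, so 194, or 582 in total.
- With continuity correction: (193.8/4) × [1 + √(1 + 2 × 3/(193.8 × 2 × 0.12))]² ≈ 206.1, so 207, or 621 in total against 620 stated. The figure reproduces.
- Recruitment margin: (700 − 620)/700 = 80/700 = 11.4%.

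**Step 2: approximate size of the seed effect.** The simulation noise of a pooled estimate, in units of its standard error, is roughly √(λ/m), where λ is the fraction of missing information. At 11.4% missing with no auxiliary predictors, λ is about 0.12.

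- m = 5: √(0.12/5) = 0.155, so z moves by about ±1.96 × 0.155 = ±0.30.
- m = 50: √(0.12/50) = 0.049, about ±0.10.
- m = 100: √(0.12/100) = 0.035, about ±0.07.

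Take combined tilted versus supine with complete-case P = 0.037 (z = 2.08). At m = 5, z runs from 1.78 to 2.39, so P runs from about 0.075 to 0.017. Simulation gives 0.017 to 0.090; the normal approximation understates the upper end because it ignores the noise in the between-imputation variance and the finite degrees of freedom. At m = 100 the approximation gives about 0.032 to 0.044, and simulation 0.032 to 0.045.

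**Step 3: the gate itself, the overall three-group test.** Observed data were held fixed and only the seed varied. Missing outcomes were imputed within arm by a logit-normal parameter draw followed by a Bernoulli draw. The 2-df test was pooled by the Li–Raghunathan–Rubin method; this is an assumption, since the protocol does not say how the overall test is pooled. The ranges shift slightly with the scale of the pooled estimate.

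Dataset: 91/206, 70/206 and 70/207. The complete-case χ² is 6.21 on 2 df, P = 0.045.

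| Imputations | 95% range of P over seeds |
|---|---|
| 5 | 0.022 to 0.116 (44% of seeds below 0.05) |
| 20 | 0.032 to 0.072 |
| 50 | 0.038 to 0.062 |
| 100 | 0.040 to 0.057 |

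A repeat run gave 0.021 to 0.114 with m = 5 and 0.038 to 0.055 with m = 100.

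**Step 4: how often it matters.** Whole trials were simulated at 46%, 34% and 34%, and each was analysed under two seeds. The figures are the share of trials in which the seeds disagree on P < 0.05.

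| Missing outcomes | m = 5 | m = 20 | m = 50 | m = 100 |
|---|---|---|---|---|
| 11.4% | 6.7% | 3.5% | 2.2% | 1.3% |
| 5% | 4.0% | – | – | – |
| 2% | 1.9% | – | – | – |

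If the middle group lies between the others (46%, 40%, 34%) at 11.4% missing, the shares are 8.3%, 3.5%, 2.5% and 1.7%.

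**Step 5: a result exactly at the design rates.** With 11.4% missing the complete-case overall P is 0.013. With m = 5 the range over seeds is 0.006 to 0.046, and 98% of seeds stay below 0.05.

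**Step 6: validity.** With no true difference, simulated rejection with m = 5 was 5.3%, so there is no sign of type I error inflation.

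**The case against.** The strongest reply is that the 11.4% is not a missing-outcome rate. Section III.F describes it only as compensation for dropouts. The primary outcome is confined to the PACU. Section III.J describes continuous monitoring, one-on-one data collectors, adhesive probes and a review of the monitor's database when the patient leaves. Section III.E has envelopes opened 10 minutes before emergence, which leaves little time for loss after allocation. Blood-gas values could still be missing, but a much lower overall rate is plausible, and at 2% missing the effect is small. This objection stands, which is why 11.4% is used here only as a likely upper bound.

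It is also fair that informative baseline predictors in the imputation model would shrink the seed effect (none were modelled here), and that a result very close to 0.05 is fragile for many reasons besides the number of imputations. The absence of a stated seed is not a defect of the protocol, since a SAP may fix it.

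Three stronger readings may tempt a reader, and the protocol does not support them:

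- *That five imputations invalidate the primary analysis.* They do not. The estimate is unbiased and the error rate holds; only reproducibility suffers.
- *That the seed is likely to decide this trial.* Even at 11.4% missing, two seeds agree in about 93% of trials at the design effect.
- *That instability of the combined-tilted-versus-supine P value shows the gate flipping.* The gate is a three-group test. At 43.0% versus 34.5% with equal tilted arms and 11.4% missing, the two-group P value straddles 0.05 across seeds, but the three-group P is about 0.12 to 0.13 and almost never crosses. The gate is sensitive only when the three-group P itself is near 0.05.

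**Conclusion.** The point holds as a minor one. The protocol itself fixes m = 5 and attaches a hard gate to the overall P value. For a borderline three-group result at 11.4% missing, the seed alone can move that P value between about 0.02 and 0.11; 50 to 100 imputations narrow this to about 0.04 to 0.06. At that missingness, going from 5 to 50 imputations cuts seed disagreement from 6.7% to 2.2% of trials, about 4.5 percentage points, and 100 brings it to 1.3%.

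These figures assume that the primary outcome is among the imputed variables, that outcomes are missing at random and equally across arms, that there are no auxiliary predictors, and that missingness equals the recruitment margin. Lower missingness or strong predictors would reduce the effect. No number of imputations removes it entirely when P lies very close to 0.05.

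**What to change.** In section III.G, replace the sentence fixing 5 imputations with one specifying at least 50, preferably 100, under a seed set before the analysis. If the SAP already fixes a seed, only the number needs changing. A pre-set seed alone would make two analysts agree, but the agreed answer would still depend on an arbitrary choice, so the larger number is the substantive part. Reporting the Monte Carlo error of the pooled primary estimate would be a useful addition and can be left to the SAP.

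The cost is one sentence and a few minutes of computing in the R package already named. The design, sample size and data collection do not change. If the imputation has already been run, it can be rerun with the larger number.

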## H. Intervention

At the end of operation, patients were transferred from operating table to transfer bed, and their positions were adjusted according to the groups.

supine position group (group S): Patients were placed in supine position from the end of surgery to leaving PACU.

15-degree semi-recumbent position group (group F): Patients were placed in 15-

---

degree semi-recumbent position from the end of surgery to leaving PACU.

30-degree semi-recumbent position group (group T): Patients were placed in 30-degree semi-recumbent position from the end of surgery to leaving PACU.

The inclination angle was set precisely by an inclinometer (GeeLii 55157, Shanghai GeeLii International Trade Co., China)

## **I. Study Procedures**

### *i. Preoperative assessment*

During the preoperative assessment, we collected baseline data include demographic characteristics, medical history, pain management history and ARISCAT scores, as well as CCI.

### *ii. Perioperative management*

Continuous monitoring was conducted for all patients through the use of electrocardiograms, noninvasive blood pressure measurements, bispectral index (BIS) electrodes (monitoring depth of anaesthesia), pulse oxygen saturation (SpO2) measurements, and end-tidal CO2 (ETCO2) measurements. Sufentanil 0.5 µg/kg, propofol 1.5 to 2.0 mg/kg, and rocuronium 0.8 mg/kg were used for anaesthesia induction. Anaesthesia was maintained with remifentanyl 0.1 to 0.3 µg/kg/min and propofol 4 to 12 mg/kg/h. After intubation, an arterial catheter was placed in the radial artery for blood gas sampling and invasive blood pressure monitoring. BIS value between 40 and 60 were maintained by adjusting the dose of propofol. The respiratory rate was initially set at 12 breaths/min and further adjusted to maintain end-tidal carbon dioxide pressure between 35 and 45 mmHg. Mechanical ventilation was maintained in a volume-controlled mode. Lung protective ventilation was used during surgery (the combination of tidal volume 8 ml/kg predicted body weight or lower and PEEP 5 cm H2O or higher, with a recruitment manoeuvre, fraction of inspired oxygen 60%) in all patients. Mean arterial pressure was maintained within ±20% of the baseline. Hypotension was treated with phenylephrine 40 µg, ephedrine 5 mg, or a fluid bolus; episodes of hypertension were managed by increasing the propofol or remifentanyl infusion rate. If the heart rate was less than 40/min, atropine 0.5 mg (i.v.)

was administered. The type and volume of fluid infusion were determined by the anesthesiologist. Rocuronium was continuously infused at a rate of 0.3 to 0.8 mg/kg/h and stopped approximately 40 minutes before the end of surgery. Postoperative patient-controlled intravenous analgesia (PCIA) was administered (sufentanil 2 µg/kg, tropisetron 10 mg, 0.9% saline diluted, the total volume of the solution is 100 ml.) and was set at 0.5 ml/press with a 15 minutes locking time. Pain scores (Visual Analogue Scale, VAS score) were assessed by nurses in the PACU. Moderate pain (VAS score 4-6) was treated with hydromorphone 0.25 mg, and severe pain (VAS score 7-10) with hydromorphone 0.5 mg, with an aim to reduce pain scores to less than 4. Once the Aldrete score was greater than or equal to 9 out of 10, the patient was discharged back to the ward.

Prior to extubation, all patients underwent suctioning, with no further stimulation being applied until spontaneous movement was observed. Neuromuscular blockade was reversed using intravenous neostigmine 40 to 60 µg/kg combined with atropine 0.5 mg. Prior to extubation the following criteria had to be met: complete reversal of neuromuscular blockade (a Train-Of-Four ratio greater than 0.90); patient fully awake; and breathing adequately.

After extubation, conventional oxygen therapy (low-flow oxygen ( $\leq 15$  l/min) delivered either by Nasal cannula,  $\text{FiO}_2$  0.35, oxygen flow 3.5 l/min; or Venturi mask,  $\text{FiO}_2$  0.35, oxygen flow 9 l/min) was administered. The recovery nurses did not intervene in the patient's breathing before the onset of hypoxemia, and only when hypoxemia occurred did the recovery nurses correct the hypoxia by encouraging the patient to take deep breaths and increasing the  $\text{FiO}_2$ . In patients who developed  $\text{SpO}_2 < 90\%$  more than 1 minutes, rescue mask ventilation was applied. A decision to re-intubate was made by the anaesthetist in the PACU if the ROX index (defined as the ratio of pulse oximetry/fraction of inspired oxygen to respiratory rate) was less than 4.88. If there was evidence of hemodynamic instability, the intervention was cancelled by the anaesthetist.

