## **J. Measurements and Endpoints**

The primary outcome was the incidence of postoperative hypoxaemia in the PACU (defined as  $\text{SpO}_2 < 90\%$  for more than 10 seconds or  $\text{PaO}_2:\text{FiO}_2$  ratio below 300 mmHg). We also recorded the incidence of severe hypoxaemia ( $\text{SpO}_2 < 85\%$  for more than 10 seconds) and the time to first episode of hypoxaemia. Patients were continuously monitored real-time vital signs in the PACU using a Mindray BeneVision N15 monitor (Shenzhen Mindray Bio-Medical Electronics Co., Ltd.). In this study, data collection was performed by one-on-one researchers in the PACU, review of the monitor's database by the data collector when the patient leaving the PACU. To avoid pulse oximeter probe dislodging the finger or having it only partially on the finger, we used disposable finger probes that stick to the finger like a Band-Aid for continuous monitoring (Disposable  $\text{SpO}_2$  Sensor, Shenzhen Mindray Bio-Medical Electronics Co., Ltd.).

The secondary outcomes included:

airway rescue (defined as the need for mask noninvasive positive pressure ventilation, or re-intubation);

respiratory symptoms (coughing);

extubation time (defined as the time from end of surgery to extubation);

respiratory comfort (before leaving PACU, graded using a numerical rating scale, ranging from 0 to 10, higher score means more comfort);

duration of stay in the PACU;

wound pain (VAS score measured at rest, while coughing at 5 and 30 minutes after extubation, before leaving PACU, and 24 hours post operation);

and position-related adverse events (hypotension, arrhythmia, and some other adverse events).

The patient's vital signs (heart rate and mean arterial pressure) were recorded at six time points: (1) the beginning of surgery (T0); (2) the end of surgery (T1); (3) immediately after adjusting position (T2); (4) immediately prior to extubation (T3); (5) 1 min after extubation (T4); (6) when leaving the PACU (T5).

Dynamic lung compliance ( $\text{C}_{\text{dyn}}$ ) and driving pressure ( $\Delta P$ ) were also recorded at

---

320 three time points: (1) when stitching; (2) 5 minutes after adjusting position; and (3)  
321 before extubation.

322 Arterial blood gas analysis was performed at three time points: (1) when stitching; (2)  
323 5 minutes after adjusting position; (3) 5 minutes post-extubation.

324

---

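### PACU wound-pain VAS is compared between arms while the same scale triggers opioid rescue and no postoperative opioid use is recorded, so later PACU pain differences are attenuated by an unknown amount

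*Protocol*

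**What the plan says.** Protocol section III.J (Measurements and Endpoints) lists, among the secondary outcomes, "wound pain (VAS score measured at rest, while coughing at 5 and 30 minutes after extubation, before leaving PACU, and 24 hours post operation".

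Section III.I.ii (Perioperative management) uses the same scale to decide treatment in the PACU:

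- The scorers are named: "Pain scores (Visual Analogue Scale, VAS score) were assessed by nurses in the PACU".
- The rule for the middle band reads "Moderate pain (VAS score 4-6) was treated with hydromorphone 0.25 mg". Scores of 7 to 10 bring 0.5 mg of the same drug. The goal stated for both bands is given as "with an aim to reduce pain scores to less than 4".
- All patients also receive a patient-controlled pump containing "sufentanil 2 µg/kg, tropisetron 10 mg, 0.9% saline diluted, the total volume of the solution is 100 ml". Its delivery, by the protocol's account, "was set at 0.5 ml/press with a 15 minutes locking time".

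On blinding, section III.E says of those who score and treat pain: "It was not feasible to blind the PACU anesthesiologists and nurses".

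Section III.J names no hydromorphone dose, rescue rate or pump consumption, either as an outcome or among the recorded measurements. The only opioid-consumption variable in the analysis (section III.G) is intraoperative, and it serves as a covariate in a post hoc logistic model. Continuous outcomes go to ANOVA or Kruskal-Wallis, and repeated measures to repeated-measures ANOVA.

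**The concern.** A pain score that is treated towards a target is not a free measure of pain. If one position leaves patients in more pain, more of them reach 4, more receive hydromorphone, and their next score falls. The difference then sits partly in the VAS and partly in the opioid given. Only the VAS part is on the protocol's list.

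The risk is a conclusion that position makes no difference to wound pain when one arm needed more opioid to get there. The listed data could not reveal this. A statistical analysis plan could define how scores after rescue are handled, but it cannot supply doses that were never collected.

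**Working it through.** **The plan's own figure.** The protocol gives no mean, SD, effect size or sample size for wound pain, so there is no pain figure to reproduce. Its sample size concerns hypoxaemia only. For 46% against 34%, 2:1 allocation, two-sided 5%, 80% power and continuity correction, the calculation gives 207 supine patients and 3 × 207 = 621 in total, against the stated 620. That agrees and does not bear on this point.

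**Pump settings (section III.I.ii).** One press delivers 2 µg/kg × 0.5/100 = 0.01 µg/kg. A 15-minute lockout allows 4 presses per hour, so at most 0.04 µg/kg/h, and 96 × 0.01 = 0.96 µg/kg in 24 hours. Consumption can vary between patients up to that ceiling, but the pump has no VAS target.

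**Illustration of the attenuation.** Only the rescue bands (4–6 and 7–10) come from the protocol. Everything else is assumed: normal scores limited to 0–10, SD 1.5 or 2, an untreated difference of 1 point before limiting, and a higher-pain arm mean of 3, 4, 5 or 6. There were 400,000 simulated scores per arm. Two drug responses were tried:

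- Full: every score of 4 or more moves to a value spread evenly over 2–4 (mean 3).
- Partial: moderate scores fall by 1 point and severe scores by 2.

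Share rescued = 1 − Φ((4 − mean)/SD). Share of difference kept = treated difference ÷ untreated difference.

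Hand check at means 5 and 4, SD 2:

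- Rescued: 1 − Φ(−0.5) = 69% against 1 − Φ(0) = 50%.
- Full response, mean 5: 0.691 × 3 + (5 × 0.309 − 2 × 0.352) ≈ 2.07 + 0.84, which is 2.92 after the small correction for the limit at 0.
- Full response, mean 4: 0.5 × 3 + (4 × 0.5 − 2 × 0.399) ≈ 1.50 + 1.20, which is 2.72 after the same correction.
- The difference is 0.20, against 0.99 untreated, so 20% is kept.

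All scenarios (SD 1.5 / SD 2):

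| Higher-arm mean | Kept, full response | Kept, partial response | Rescued, higher vs lower arm |
|---|---|---|---|
| 3 | 66% / 57% | 83% / 81% | 25 vs 9% / 31 vs 16% |
| 4 | 37% / 38% | 73% / 75% | 50 vs 25% / 50 vs 31% |
| 5 | 12% / 20% | 68% / 71% | 75 vs 50% / 69 vs 50% |
| 6 | 0% / 7% | 68% / 70% | 91 vs 75% / 84 vs 69% |

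The direction is the same in every row. The loss runs from 17% (100 − 83) to about 100%. In these scenarios it exceeds half only when rescue fully succeeds and mean untreated pain in the worse arm is 4 or more. In every row the arms differ in rescue use, which no listed outcome would show.

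**Which time points.** Five minutes after extubation probably precedes most rescue. The scores at 30 minutes and before leaving the PACU fall in the rescue period. At 24 hours only the pump is described. The protocol does not say whether the resting or the coughing score triggers rescue. If it is the resting score, coughing scores are less tightly controlled.

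**The case against.** The strongest reply is that VAS as observed under a common pain protocol is a legitimate treatment-policy comparison. It asks whether position leaves patients in more pain under usual care. Pain is one of seven secondary items, has no hypothesis of its own, and post-rescue handling may sit in an analysis plan not shown here. That stands, and it is why the point asks for added data and not a different endpoint. It does not remove the gap, because the treatment-policy result cannot be interpreted without knowing how much opioid each arm received.

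A reader might infer two stronger things.

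- **That a real pain difference is largely erased and all later scores are forced together.** The documents do not support this. The protocol states an aim, with one dose per pain band, and neither a repeat-dosing rule nor assured success. With partial response, 68–83% of the difference survives. No VAS target is described at 24 hours, and the early PACU score is largely intact.
- **That unequal PACU opioid is a competing explanation for the hypoxaemia result.** Opioid given after allocation under one common rule is a consequence of allocation and possibly part of the pathway. It does not confound the intention-to-treat comparison. The blood-gas component is also sampled 5 minutes after extubation, when little rescue is likely to have acted.

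A further reply is that a score must be taken before a rescue dose can be chosen, so the triggering score is already pre-rescue. That is true at that moment. However, the protocol does not tie the scheduled scores to the triggering ones, and carry-over from earlier doses remains.

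**Conclusion.** The point holds in a limited form. VAS comparisons at 30 minutes and before leaving the PACU are attenuated towards no difference, by an amount the documents leave open: from about 17% to nearly all of an assumed 1-point difference. The listed measurements cannot show where the missing part went. The 5-minute score is probably little affected, and at 24 hours the effect is limited to whatever patients self-administer.

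The percentages rest wholly on assumed means, SDs and drug responses. The direction rests on the rescue rule being applied alike in all arms. The nurses who apply it are unblinded, so this is not guaranteed, which is a further reason to report doses by arm. This is a matter for one secondary outcome. The primary analysis and the sample size are unaffected.

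**What to change.** 1. Add two outcome lines by arm: PACU hydromorphone (any use and total dose) and patient-controlled sufentanil consumed to 24 hours. Report them beside VAS.
2. State that each scheduled PACU VAS is taken before any rescue dose given at that time point.
3. State that similar VAS scores alone will not be read as no difference in pain. A joint rank of VAS and opioid use may be added as a supportive analysis, but it is optional.
4. Present PACU opioid use by arm as descriptive context for the hypoxaemia result. Do not adjust the primary analysis for it.

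The analgesic regimen, sample size and primary intention-to-treat analysis stay unchanged. The cost is modest data extraction, since section III.J already places one-on-one researchers in the PACU. That doses are charted and held in the pump memory is an assumption. If patients have already been treated, as the protocol's past tense suggests, those records are the only source. If they cannot be recovered, the limitation should be stated with the pain results.
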